
### Participant timeline {13}

The time schedule of recruitment, screening and enrolment, and study session visits is shown in Fig. 2.

**Fig. 2 Fig2:**
[figure not shown]
Participant timeline. Washout time in between study session visits is at least 7 days

### Sample size {14}

For sample size estimation and power calculation, we analyzed untouched saliva samples of a previous sleep deprivation study, in which participants underwent 40 h of prolonged wakefulness and a control condition including 8 h of sleep in random, crossover fashion [27]. We detected more than 50 metabolic features showing a significant (*p* < 0.05, paired *t*-test) difference between the sleep deprivation and control conditions (unpublished observation). Utilizing the results of preliminary analysis for a power calculation (*α* = 5%, *β* = 20, thus the power of 80%), a sample size of 17 participants will be sufficient to detect significantly different metabolite quantities (*p* < 0.05). As the presented study setting offers several improvements for meeting the defined outcome goals, a smaller sample size may be appropriate. Nevertheless, taking into account a few possible dropouts of participants (e.g., risk of driving simulator sickness) and organizational aspects (number of available beds in sleep research laboratory per session is four, adequate supervision, etc.), and ultimately assuring ourselves to perform a sufficiently powered study, we aim to recruit 24 participants.

For comparison, relevant completed trials with comparable protocols had sample sizes between 10 and 16 (10 male, 12 male, 12 female, and 16 (eight men)) [28–31].

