## Statistical methods

### Statistical methods for primary and secondary outcomes {20a}

Based on our study design, statistical analysis will be performed to detect both intra- and inter-individual (i.e., individual and group) differences. All the analyses will be carried out in reference to hours of wakefulness (i.e., clock time), and also in reference to the internal body time (IBT) of the participants which is determined by the dim light melatonin onset (DLMO) from oral fluid samples.

The primary outcome of the trial is the changes detected in the metabolome. Concentration values of metabolic features will be used to generate feature time series. As a first characterization, the rhythmicity of features will be tested by cosinor analysis. Other regression models such as linear, exponential, or logarithmic functions will be applied for fitting time series data in order to simplify complex patterns. To extract relevant features from the time series, different statistical approaches will be carried out. Firstly, we will investigate how group-level differences vary when applying generalized linear mixed models and — if group-level differences exist — conduct multiple comparison tests. After applying the corrections for multiple testing (Benjamini–Hochberg procedure, i.e., false discovery rate), adjusted p-values will be considered significant when below 0.05. Significant features will then be shortlisted. Secondly, each time series will be checked for the occurrence of regular patterns (e.g., linear increase/decrease, exponential, etc.) in relation to hours of wakefulness. Again, each feature candidate will be added to the shortlist. Lastly, a classification task will be carried out to isolate those features leading to a separation between the study arms. The result of the primary outcome will be a list of candidate biomarkers.

For secondary outcomes, differences between study groups will be reported. For variables that are continuous (i.e., outcome of PVT, d2-task, driving simulator parameters, EEG data) the mean and the median will be computed accordingly. For variables that are either binary or ordinal (i.e., results of the behavioral impairment test, visual attention test, sleepiness scales, expert decision on driving ability), the relative frequencies, proportions, and standard errors for each group will be reported.

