## Discussion

To the best of our knowledge, this is the first trial of its kind that investigates complete metabolic profiles combined with performance monitoring in humans over a multi-day period involving different sleep–wake schedules (control, sleep deprivation, and sleep restriction conditions in the same participants). Hereby, we aim to establish a candidate biomarker panel being indicative for sleepiness and its behavioral outcomes. For that purpose, established validated performance tests**,** as well as actual driving ability in a highly sophisticated driving simulator will be assessed. Driving simulation will be tested in the early morning hours, which is the peak time of sleep-related car crashes [5, 32]. Thus, by mimicking real-world scenarios, we believe that the generalization of our findings will be well justified. Nevertheless, our intended candidate biomarker panel will have to be verified by routine case samples to be tested for ruggedness towards confounding factors. Since the study only includes men, it remains to be seen whether the biomarker panel also works for women. We decided to recruit only male volunteers due to the strong menstrual cycle’s implications on the female metabolome [30]. However, as sleep–wake regulation represents a fundamental structure not just in humans, we assume that robust markers should exist and can be detected by our study. Taking into account that young males represent the most vulnerable target group of microsleep-related car accidents (compare {6a}), this does not necessarily mean a limitation of study results. In this trial, we chose to apply strict inclusion and exclusion criteria as well as tight control and supervision. In doing so, we hypothesize detecting relevant markers in less than 20 participants. Although the physiological principles underpinning sleep–wake regulation are generalizable, the current findings will be applicable only to healthy young men who form the highest-risk group for sleepiness-induced road traffic accidents. We are convinced that they will expand our knowledge of candidate biomarker panels of sleep–wake regulation in humans. Nevertheless, future studies in larger samples will have to examine whether the findings can be generalized to the general population and to an uncontrolled environment.

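### The 80% power at 17 participants is set at an unadjusted 5% level, while the group-comparison step of the primary analysis declares features only after Benjamini–Hochberg adjustment; the figure should be restated under that rule

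*Protocol article*

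**What the plan says.** **Planning criterion.** Sample size {14} draws on saliva samples from an earlier study in which "participants underwent 40 h of prolonged wakefulness and a control condition including 8 h of sleep in random, crossover fashion". It reports: "We detected more than 50 metabolic features showing a significant" difference between conditions, judged by a paired t-test at p < 0.05. The next sentence begins "Utilizing the results of preliminary analysis for a power calculation", takes alpha at 5% and power at 80% (beta is printed as 20, read here as 20%), and concludes that "a sample size of 17 participants will be sufficient to detect significantly different metabolite quantities", again at p < 0.05. No adjustment for multiple testing is mentioned. The section adds that, because of improvements in the study setting, "a smaller sample size may be appropriate", and then sets recruitment at 24.

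**Analysis criterion.** Outcomes {12} covers all metabolites that can be detected, and Plans for assessment and collection of outcomes {18a} describes the assay as untargeted. Statistical methods {20a} fits generalized linear mixed models, follows with multiple comparison tests, applies the Benjamini–Hochberg procedure and says "adjusted p-values will be considered significant when below 0.05". Two further routes to the shortlist, regular time patterns and a classification task, state no false discovery rate threshold.

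**Related statements.** The Discussion says "we hypothesize detecting relevant markers in less than 20 participants". Sequence generation {16a} treats 18 as the minimum sample size. Trial status lets recruitment end in June 2023 even if 24 participants have not completed.

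**The concern.** The planning criterion and the analysis criterion are both printed in the article, and they differ. An effect that is detected with 80% probability at an unadjusted 0.05 is detected less often once the p-value must survive a false discovery rate correction over many features. A reader who takes the 80% at face value will overrate what 17 or 18 completers can deliver on the group-comparison route. This matters in practice because 18 is built into the allocation as a minimum and recruitment can close before 24.

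Two features of the pilot bear on the same figure. If the planning effect was taken from the features that reached p < 0.05, it is biased upward by that selection. The pilot also compared prolonged wakefulness with control, so it offers no direct basis for the power of sleep restriction versus control, which is one of the trial's two sleep-deficit comparisons.

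**Working it through.** **Inputs from the article:** alpha 5%, power 80%, n = 17, target 24, minimum 18, Benjamini–Hochberg at 5%. **Assumed, because not stated:** two-sided paired t-test, the same effect in every truly changed feature, independent features, and a range for the share of features that truly change.

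**Step 1: the plan's own figure.** With no effect size or standard deviation given, 17 cannot be reproduced forward. Solved backward from the noncentral t distribution (16 degrees of freedom, noncentrality dz × √17), 80% power at two-sided 0.05 needs dz = 0.724. A one-sided test would give 0.630, and the normal approximation 0.679. At unadjusted 0.05 the same dz = 0.724 gives 82% at n = 18, 87% at n = 20 and 92% at n = 24.

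**Step 2: direction.** If R of m features are declared, the Benjamini–Hochberg cut-off is 0.05 × R/m. This is below 0.05 unless every feature is declared. For the effect that gives 80% at n = 17, power under the adjusted rule is therefore below 80% for any m.

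**Step 3: size.** Let π be the share of features that truly change. The large-sample cut-off t solves

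t = 0.05 × [(1 − π) × t + π × power(t)].

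Example, n = 17 and π = 0.5: t = 0.0158 and power = 0.617. Check: 0.05 × (0.5 × 0.0158 + 0.5 × 0.617) = 0.0158.

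Example, n = 24 and π = 1/3: t = 0.0138 and power = 0.80. Check: 0.05 × (0.667 × 0.0138 + 0.333 × 0.802) = 0.0138.

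Average power per truly changed feature, dz = 0.724:

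| Share changed | n = 17 | n = 18 | n = 20 | n = 24 |
|---|---|---|---|---|
| 90% | 74% | 78% | 83% | 91% |
| 50% | 62% | 67% | 74% | 85% |
| 33% | 52% | 58% | 67% | 80% |
| 20% | 40% | 46% | 56% | 72% |
| 10% | 24% | 30% | 41% | 60% |
| 5% | 12% | 16% | 27% | 47% |

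Simulation with 1,000 independent features agrees: at n = 17, 74%, 62%, 40% and 14% for shares of 90%, 50%, 20% and 5%; at n = 24, 91%, 85%, 72% and 46%. The large-sample formula is too pessimistic in extreme cases. With 50 of 5,000 features changed and n = 17 it gives 0.5%, against about 2 to 3% by simulation.

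**Step 4: detectable effect with 24 completers.** For 80% average power the cut-off is t = 0.05 × 0.8 × π / [1 − 0.05 × (1 − π)]. For π = 0.5 this is 0.02 / 0.975 = 0.0205. The dz detectable at n = 24 is then 0.69 (half change), 0.72 (a third), 0.77 (20%), 0.83 (10%) and 0.89 (5%).

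**Step 5: selection in the pilot.** A paired t-test reaches p < 0.05 only if the observed |dz| exceeds t(0.975, n − 1)/√n. For a pilot of 8 to 20 participants (assumed; the size is not stated) that bound runs from 0.84 down to 0.47. If the true dz were 0.3 and the pilot had 12 to 20 participants, the mean observed |dz| among the features selected would be 0.85 down to 0.62.

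**The case against.** The strongest reply is that the trial is labelled exploratory, aims at a list of candidates that must later be verified, and recruits 24 rather than 17. On that view, recovering 80% of all changed features is not the goal. Much of this stands:

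- A reader might infer that most true features will be missed. The article does not support that at 24 completers: about 70% are found with 50 of 300 features changed, and 80% if a third of features change.
- A reader might infer that a short list will be taken as absence of markers. That is weak. In simulations at n = 24 with 50 changed features, at least one true discovery was practically certain with 300 or 1,000 features, and about 95 to 98% likely with 5,000.
- The mixed models use repeated samples and may be more efficient than one paired t-test, and the other two shortlist routes state no such threshold. The figures above are therefore not the power of the whole primary analysis. Equally, the article quantifies none of this, and it does not make an unadjusted figure match the adjusted rule.
- A reader might take it as established that the planning effect came from features selected as significant, or that the pilot's hits were chance. Selection is the natural reading of two consecutive sentences but is not stated outright. The number of pilot features tested is not given, and a condensed article need not give it.
- The remark on a smaller sample is justified by an improved study setting, and the expectation of fewer than 20 by strict eligibility and control. Neither rests only on the figure of 17, and the second is a hypothesis about finding markers, not a claim of 80% power.
- The article claims no power specific to sleep restriction, and it matches the two deficit arms on total sleep loss (8 h). The lack of a direct power basis for that contrast is a limit to state, not an error.

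What the reply does not remove is that the 80% is printed as the basis for sufficiency at 17, under a criterion that the group-comparison step does not apply.

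**Conclusion.** The point holds as a mismatch between planning and analysis, and it should be fixed. For the effect implied by 17 participants, 80% average power is not delivered at n = 17 on the Benjamini–Hochberg route, whatever the number of features. How far it falls short cannot be fixed from the article: from 74% down to 12 to 14% over the range considered. At 24 completers, 80% is kept if roughly a third or more of the features truly change and lost if fewer do.

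These figures assume a two-sided paired t-test, a common dz of 0.724 and independent features. If the planning effect was taken from significant pilot features, the true effects are smaller and power is lower still. No arithmetic error in the number 17 is shown, since its effect size is not given. The stronger conclusion that a trial of 24 is underpowered is not supported.

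**What to change.** Keep 24 participants and change the text of Sample size {14}:

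1. Rerun the calculation on all pilot features, not only those with p < 0.05, with the Benjamini–Hochberg rule at 5%.
2. Report average power at a 5% false discovery rate, or the dz detectable with 80% average power, for 24 and for about 18 to 20 completers. State the number of features and the changed share assumed.
3. Say that the figure applies to the sleep deprivation contrast and to the Benjamini–Hochberg route only, and that sleep restriction versus control has no direct power basis.
4. Qualify the remark that "a smaller sample size may be appropriate" as not supported by a power calculation under the false discovery rate rule.

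The cost is one rerun on existing pilot data and a rewritten paragraph. Design and analysis stay as they are and no participants are added. The downside is that the stated power becomes less favourable.

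### The 80% power at 17 participants is for an unadjusted 5% test per metabolite, not for the Benjamini-Hochberg rule used in the planned group comparison

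*Protocol article*

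**What the plan says.** Section {14} of the protocol article bases the sample size on stored saliva from an earlier crossover study in which "participants underwent 40 h of prolonged wakefulness and a control condition including 8 h of sleep in random, crossover fashion". It reports: "We detected more than 50 metabolic features showing a significant (*p* < 0.05, paired *t*-test) difference between the sleep deprivation and control conditions". From these results, with alpha 5% and "thus the power of 80"%, it concludes that "a sample size of 17 participants will be sufficient to detect significantly different metabolite quantities", again at p below 0.05. It gives no effect size, no standard deviation of the paired differences, no count of features tested and no allowance for multiplicity. The target of 24 is then explained by possible dropouts, bed capacity and the wish for adequate power.

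Section {20a} sets out how candidate biomarkers are found in oral fluid:

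- **Group comparison.** Generalized linear mixed models are followed by multiple comparison tests. After Benjamini-Hochberg correction, "adjusted p-values will be considered significant when below 0.05", and the significant features are shortlisted.
- **Pattern check.** Features whose time series follow a regular pattern over hours of wakefulness are also added to the shortlist.
- **Classification.** A classification task isolates features that separate the study arms.

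Only the group comparison carries a significance rule with a multiplicity correction.

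**The concern.** The power statement and the group comparison use different decision rules. Section {14} counts a metabolite as detected when its own p-value is below 0.05. The group comparison in {20a} counts it as detected only when its adjusted p-value is below 0.05, which in an untargeted analysis of many features can be far stricter. A reader who takes 80% as the chance of detecting a true marker in the group comparison is misled, even for the contrast the pilot studied.

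What is at stake is how the result is read. If the group comparison yields few features, the claim of adequate power invites the conclusion that few markers exist, when many true markers of the planning size could have been missed. The figure of 17 also matters in practice. Section {16a} treats 18 as reaching the minimum sample size, the Discussion expects markers in fewer than 20 participants, Trial status lets recruitment end in June 2023 before 24 have completed, and {18b} excludes all outcome data when the sleep regime is not followed.

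**Working it through.** **Inputs from the article.** n = 17, alpha 5%, power 80%, paired t-test at p < 0.05 in the pilot, and a target of 24 (all {14}); Benjamini-Hochberg adjusted p < 0.05 ({20a}).

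**Assumptions, not in the article.** Two-sided test; one common effect for all true features; independent features; correction across all m features tested; m = 200, 500, 1000 or 2000; 50 truly changed features (a round number suggested by the pilot count, which counts unadjusted hits and not true effects).

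**Step 1: the plan's own figure.** Without an effect size, 17 can be neither reproduced nor refuted. It can be inverted. For a paired t-test, power = P(T > t(1 − α/2, n − 1)), where T is noncentral t with n − 1 degrees of freedom and noncentrality dz·√n. With n = 17, the critical value is 2.120. Power 80% requires dz·√17 = 2.985, so dz = 2.985/4.123 = 0.724. At this dz the unadjusted power is 80% at n = 17 and 92% at n = 24.

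**Step 2: direction.** With R features declared significant out of m, the Benjamini-Hochberg cut-off on the raw p-value is 0.05·R/m. Since R ≤ m, it never exceeds 0.05. For the same test and effect, power cannot exceed the unadjusted figure. Even if every feature truly changed, average power at n = 17 would be 75%.

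**Step 3: size.** Let π be the share of features that truly change. For large m the cut-off t solves t = 0.05·[(1 − π)·t + π·power(t)]. For example, with π = 50/500 = 10% and n = 24, t = 0.05 × 0.10 × 0.60/(1 − 0.05 × 0.90) = 0.0030/0.955 = 0.0031, and the paired t-test has power 60% at that cut-off.

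Simulation with 50 true features gives these average powers per true feature:

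| Features tested (assumed) | 24 completers | 17 completers |
|---|---|---|
| 200 | about 76% | about 45% |
| 500 | about 60% | about 25% |
| 1000 | about 47% | about 13% |
| 2000 | about 34% | about 7% |

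**Step 4: when 80% is reached.** From the same equation with 24 completers, average power is 60% at π = 10%, 72% at 20%, 78% at 30% and 85% at 50%. So 80% needs somewhat more than 30% of features to change. The n for 80% is 22 at π = 50%, 27 at 20%, 31 at 10% and 35 at 5%.

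**The case against.** Several points on the other side stand.

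- **Other routes.** A reader might infer that no feature reaches the candidate list without passing the Benjamini-Hochberg rule. Section {20a} does not say so: the pattern check adds features and the classification task selects them with no such condition. The point is therefore limited to the group comparison. These routes do not rescue the 80%, because {14} speaks of significant differences and no power is stated for the other routes.
- **An empty result.** A reader might infer that the group comparison is likely to find nothing. The scenarios do not support that at planned enrolment. With 1000 features the chance of no discovery is about 6% at n = 17 and essentially 0% at n = 24.
- **How strict the cut-off is.** It need not be orders of magnitude below 0.05. With 200 features the mean cut-off is about 0.0059 at n = 17 and 0.0099 at n = 24, so it is lower by a factor of about 8 and 5.
- **A different test.** The planned mixed model uses repeated samples per condition, and its power may differ from that of one paired t-test. The article claims no such gain in its calculation, so this makes the size uncertain without supporting the 80%.
- **Scenarios only.** The number of features, the true share, the common effect and independence are all assumed.
- **Exploratory aim.** Section {8} calls the trial exploratory, and the Discussion says the panel must still be verified. No confirmatory claim depends on the 80%.

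**Conclusion.** The mismatch is real, and the article alone shows it: the 80% at 17 belongs to an unadjusted 5% test per feature, while the group comparison decides on Benjamini-Hochberg adjusted p-values. The direction does not depend on the number of features. The size does. At the implied effect of 0.72, the scenarios with 50 true features run from about 76% down to 34% with 24 completers and from about 45% down to 7% with 17, while a large share of truly changed features would bring 24 completers above 80%.

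This does not show an arithmetic error in the 17, nor that 24 participants are too few for the study's aim. It shows that the stated power describes a rule other than the one used in the group comparison. Severity is moderate, because the trial is exploratory and produces candidates for later verification.

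**What to change.** In {14}, label the 80% as power per feature for a paired t-test at an unadjusted 5%. Add the average power under Benjamini-Hochberg at 5% for the number of features the pilot pipeline tested, at 24 and at 17 completers, with the assumed share of true features. Alternatively, give the standardised difference that reaches 80% under that rule with 24 completers. Keep the claim of adequate power only if the new figure supports it, and state that the pattern and classification steps have no power calculation.

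The cost is one recalculation from the pilot feature table and a reworded paragraph. The stated power becomes less favourable. Enrolment does not change.

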### Recruitment {15}

Recruitment of volunteers will be accomplished by a three-step escalation plan. Firstly, premises, networks, and extensive media channels of the University of Zurich and local schools will be used for advertisement of the trial. As a second means, public spaces and displays in Zurich will inform about the open recruitment status. Lastly, trial information can be spread via partner universities and public media channels over the whole Switzerland and Southern Germany. The recruitment period is scheduled from November 2022 until June 2023.

